## Methods

### Design

This wheat intervention study will characterize the variable response of gut bacteria to supplementation in adult humans. Treatments will include (1) refined soft white wheat flour, (2) bran-containing whole-wheat flour of Michigan soft white wheat, or (3) bran-containing whole-wheat flour of Michigan soft red wheat. All 3 flour samples will be provided by King Milling Company (Lowell, Michigan). Each of the two whole-wheat interventions will be administered over a 1-week period, with a baseline week (refined soft white wheat flour) before the intervention begins and a washout week (refined soft white wheat flour) between the two test periods (Figure 1). Wheat flour will be administered to participants in the form of wheat crackers. The nutrient composition of the wheat crackers is provided (Table 1)**.** During each of the two test periods, 80 g of crackers made from whole-grain soft white wheat flour or whole-grain soft red wheat flour will provide each participant with approximately 10.7 g of total dietary fiber per day (Table 1). At the end of each 1-week treatment period, a stool sample as well as answers to a health and fiber intake questionnaire, will be collected from each participant. A total of 4 stool samples will be collected from each participant over the course of the study. Microbiome samples will be aliquoted and stored at −80°C until analysis.

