### Setting and Participant Recruitment

This study will be conducted during the summer in East Lansing, Michigan, on the campus of Michigan State University and will enroll 30 adults. Subjects will be recruited via flyers hung in buildings around the Michigan State University campus as well as through the Michigan State University–paid research pool [31]. To be included in the study, participants must be aged between 18 and 55 years as the gut microbiota matures by adulthood and remains stable throughout [1]. Participants must also have bowel movements at least once every 3 days, be willing to eat wheat crackers, and be available for weekly lab visits. Participants will be excluded if they take any nonsteroidal anti-inflammatory drugs, antacids, proton pump inhibitors, nutritional supplements, or multivitamins daily; have taken any antibiotics in the 2 weeks before the study; have gastrointestinal issues or diabetes; are pregnant; are following any special diet; or have food allergies. Participants will be provided with a US $50 cash incentive upon completion of the dietary intervention. All participants will provide written informed consent.

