### Statistical Analyses

Statistical analysis of differences between pre- and posttests will be assessed using ANOVA or Friedman Wilcoxon rank-sum tests [39]. Multivariate statistics will be performed using R (R Foundation for Statistical Computing), a free statistical software program. To compare the alpha diversity of the microbial communities, Chao1 (a measure of richness), inverse Simpson (a measure of richness and evenness, with emphasis on evenness), and Shannon diversity (a measure of richness and evenness, with emphasis on richness) will be calculated in R using the vegan package [40]. ANOVA and Wilcoxon signed-rank test or Friedman test with post hoc comparisons will be used to compare alpha diversity across treatment categories after intervention [41]. For beta diversity, Bray-Curtis and Sorenson distances will be used with principal coordinates analysis ordination to produce plots of the distances between samples. Differences in beta diversity between time points will be determined using permutational multivariate ANOVA (PERMANOVA) via the adonis function in the vegan package, and differences in group dispersion will be determined using PERMDISP [40]. PERMANOVA may also be used to determine the relationship between the distance metrics and wheat variety, as well as other variables. Metastats (a function of the mothur software package) will be performed on the subsampled abundance data to test for significant differences in operational taxonomic unit abundance between groups [42]. Changes in taxa (both genus and phylum level) >1% average relative abundance will be determined across time points using the Friedman test with post hoc comparisons. Where appropriate, the negative binomial and zero-inflated mixed models in the R package will be used to test for differences in taxa abundance over time [43].

Enterotypes will be manually assigned based on clustering within quadrants in a Bray-Curtis principal coordinates analysis plot overlaid with the most abundant taxa driving community differences, as in Wu et al [4], using the envfit function in the vegan package. Significant differences between enterotypes will be determined using ANOVA for parametric data and the Kruskal-Wallis test for nonparametric data. Differences between time points within each enterotype will be determined using the Friedman test with post hoc comparisons.

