### Response Analysis

If only a subset of participants is found to respond to the treatment, response groups will be determined by an individual’s change in alpha diversity metrics across the treatments. A participant will be considered a *positive responder* if alpha diversity (either Chao1, Shannon, or inverse Simpson) is greater at time points B and D (whole wheat) than at both A and C (refined white wheat). However, if this change is not observed, participants will be considered *nonresponders*. After post hoc assignment of response groups, differences in overall alpha diversity between positive responder and nonresponder groups will be tested with ANOVA (if parametric) or Wilcoxon ranked-sum (if nonparametric). The normality of data will be determined using the Shapiro-Wilk test. Differences will be tested within each time point. Beta diversity differences between response groups will be determined at each time point using PERMANOVA and PERMDISP. Continuous demographic variables (age, BMI, and fiber intake) will be compared with a two-tailed *t* test if parametric and a Wilcoxon rank-sum test if nonparametric, with normality confirmed using the Shapiro-Wilk test. The Fisher exact test will be used to determine the independence of sex, smoking exposure, and race regarding response to treatment. Differences in genera present at >1% average relative abundance will be tested between response groups using a negative binomial model in the MASS package [44].

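### PERMANOVA on four repeated samples per person is planned with no participant term or permutation restriction: unrestricted, it is conservative for time point and wheat variety and anti-conservative for variables that are stable within a person

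*Protocol article*

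**What the plan says.** All places are in the Methods of the protocol article.

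- **Setting and Participant Recruitment:** the study is to take place "on the campus of Michigan State University and will enroll 30 adults".
- **Design:** "A total of 4 stool samples will be collected from each participant over the course of the study". At full retention this is 30 × 4 = 120 samples.
- **Statistical Analyses**, specified use: "Differences in beta diversity between time points will be determined using permutational multivariate ANOVA (PERMANOVA) via the adonis function in the vegan package".
- **Statistical Analyses**, optional extension: "PERMANOVA may also be used to determine the relationship between the distance metrics and wheat variety, as well as other variables". The other variables are not listed. Nothing says whether their tests pool the four samples, and no participant term, blocking or permutation unit is given for either use.
- **Response Analysis**, community comparison: "Beta diversity differences between response groups will be determined at each time point using PERMANOVA and PERMDISP". Each such test uses one sample per person.
- **Response Analysis**, genera: "Differences in genera present at >1% average relative abundance will be tested between response groups using a negative binomial model in the MASS package". This sentence carries no time-point restriction and names no participant effect.

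Repeated samples are handled openly elsewhere. Butyrate Gene Analyses uses a repeated-measures ANOVA. Statistical Analyses uses Friedman tests for taxa across time points, and mixed models for taxa over time where appropriate.

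**The concern.** A permutation test is valid when the units it shuffles are exchangeable under the null hypothesis. Four samples from one person resemble each other, and the article itself relies on this when it counts within-person comparison among its strengths (Strengths and Weaknesses). Shuffling all 120 rows treats them as exchangeable when they are not.

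The error depends on the kind of variable:

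- For a factor that varies within a person (time point, wheat variety), differences between people stay in the residual. The test loses power, so a real effect of wheat on community composition could be missed.
- For a variable that is constant or nearly so within a person, differences between people leak into its effect. The test rejects because people differ, whether or not the variable matters.

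No single permutation setting serves both. Permuting within participant corrects the first case, but for a variable that is constant within a person every such permutation leaves the data arrangement unchanged, so the p-value is always 1. The plan therefore has to distinguish the two kinds of variable.

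**Working it through.** **Inputs.** From the article: 30 participants, 4 samples each, adonis, Bray-Curtis distance. Assumed, because the article gives none of them: nominal level 5%, ICC from 0 to 0.9, number and evenness of taxa. The plan states no figure for this test, so there is none to reproduce.

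**Step 1: direction, for a single response.** Let total variance be 1, of which ρ lies between people.

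- Person-level factor: expected mean square = (1 − ρ) + 4ρ = 1 + 3ρ, against a pooled residual of about 1. The false-positive rate is about P(|Z| > 1.98/√(1 + 3ρ)). At ρ = 0.3: 1.98/√1.9 = 1.44, giving 0.15. At ρ = 0.5: 1.98/√2.5 = 1.25, giving 0.21. Simulation (40,000 runs) gave 0.155 and 0.218.
- Within-person factor: expected mean square = 1 − ρ, again against about 1. The ratio is below 1 whenever ρ > 0, so the test is conservative.

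With many taxa, the pseudo-F averages over them and its permutation distribution tightens around 1. Both errors then grow, so the number of taxa matters.

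**Step 2: PERMANOVA simulation.** Log-normal abundances of 60 fairly even taxa with a shared person effect, Bray-Curtis, 199 permutations, 200 runs per row, no true effect of anything. The person-level factor is binary (15/15). Entries are rejection rates at 5%.

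| ICC | Person-level, free | Person-level, whole participants | Person-level, one time point | Time point, free | Time point, within participant |
|---|---|---|---|---|---|
| 0 | 0.04 | 0.04 | 0.045 | 0.03 | 0.03 |
| 0.1 | 0.155 | 0.055 | 0.025 | 0.035 | 0.065 |
| 0.3 | 0.485 | 0.03 | 0.045 | 0.00 | 0.04 |
| 0.5 | 0.745 | 0.05 | 0.06 | 0.00 | 0.055 |
| 0.7 | 0.92 | 0.045 | 0.045 | 0.00 | 0.045 |
| 0.9 | 0.96 | 0.05 | 0.055 | 0.00 | 0.06 |

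The Monte Carlo standard error at 0.05 is √(0.05 × 0.95/200) = 0.015, so the restricted schemes are compatible with the nominal level. A continuous person-level covariate gave similar free-permutation rates (0.19 at ICC 0.1, 0.905 at ICC 0.7).

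**Step 3: sensitivity.** 150 runs per setting, binary factor, free permutation, ICC 0.3 to 0.9:

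- 3 taxa: 0.17 to 0.41
- 10 taxa: 0.24 to 0.73
- 60 very uneven taxa: 0.34 to 0.70

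A three-level factor split 18/8/4 gave 0.36 to 0.94 over the same settings.

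**Step 4: weekly variables with a personal component.** Other Measurements lists weight, water source, 24-hour diet and a fiber score, collected each week. A null covariate that changes weekly was simulated (300 runs, 60 taxa):

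- Covariate ICC 0: free permutation rejected 4–5%, which is nominal.
- Covariate ICC 0.5: 46%, 79% and 87% at community ICC 0.3, 0.5 and 0.7.
- Covariate ICC 0.8: 79–98%.
- Permuting whole participants gave 3–6% for these covariates.

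**Step 5: genus comparison.** If the four samples were pooled in a negative binomial model without a participant effect, rejection under no group difference was 18% to 41% (between-person SD 0.3 to 0.8 and within-person SD 0.5 on the log scale, 400 runs per setting).

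**The case against.** A reader might infer that the plan will test sex, race, smoking, age and BMI on 120 pooled samples and mostly produce false associations. The article does not support that.

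- Those variables appear only in Response Analysis, with one-record-per-person tests against response group: "The Fisher exact test will be used to determine the independence of sex, smoking exposure, and race regarding response to treatment"; "Continuous demographic variables (age, BMI, and fiber intake) will be compared with a two-tailed *t* test if parametric". No sentence ties them to PERMANOVA, and the weekly variables fit the phrase about other variables at least as well.
- The one between-person PERMANOVA that is specified is run at each time point, which is sound.
- A majority of false positives needs a substantial ICC and many taxa, or a factor with several levels. The documents give neither the ICC nor the taxa structure.
- The extension is optional and touches neither alpha diversity nor the inflammation biomarkers.
- The genus sentence does not say that samples are pooled. An earlier sentence in that section restricts testing to each time point, although it follows the alpha-diversity test and does not settle the genus test.

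These points stand and limit the claim.

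The further argument, that an article may leave the permutation scheme to a fuller plan, carries less weight. The article names the function and says how repeated samples are treated for several other analyses, yet gives no such provision where validity depends on it. Reading the other variables as weekly ones does not remove the problem either, since a weekly variable with a strong personal component is affected too (step 4).

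**Conclusion.** The concern holds in a conditional, two-sided form. As written, with no participant term and no permutation restriction, PERMANOVA on the repeated samples gives p-values that are too large for time point and wheat variety and too small for variables stable within a person. The first affects the beta-diversity comparison actually specified: rejection was 0 of 200 at every ICC of 0.3 or more, against 4–6% when permuted within participant. The second affects the optional extension: roughly 15% to over 90% false positives for ICC 0.1 to 0.9, lower when few taxa carry the variation and nominal at ICC 0.

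These sizes rest on unrestricted permutation of all 120 samples and on assumed ICCs and taxa structures. Only the directions follow from the design. The genus point is weaker: it applies only if samples are pooled, which the article neither states nor rules out. The primary outcome is not affected.

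**What to change.** In Statistical Analyses, state the permutation unit by type of variable:

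- **Time point, wheat variety, and within-person effects of weekly variables** (fiber score, diet diversity): permute samples within participant.
- **Variables fixed for a participant:** permute whole participants, moving all four samples together, or test one time point at a time, as Response Analysis already does for response groups. One time point at a time is simpler if some participants lack a sample, because whole-participant swaps need equal numbers of samples.
- Name the other variables and assign each to one of these types.

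In Response Analysis, state that the negative binomial genus comparison is run at each time point, or use the mixed model already planned for taxa over time, with a participant effect.

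The cost is a few sentences and a changed permutation argument in software already named. No new data are needed. Fewer participant-level associations will reach nominal significance, and the time-point and wheat comparisons should regain power.

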### Response Analysis

If only a subset of participants is found to respond to the treatment, response groups will be determined by an individual’s change in alpha diversity metrics across the treatments. A participant will be considered a *positive responder* if alpha diversity (either Chao1, Shannon, or inverse Simpson) is greater at time points B and D (whole wheat) than at both A and C (refined white wheat). However, if this change is not observed, participants will be considered *nonresponders*. After post hoc assignment of response groups, differences in overall alpha diversity between positive responder and nonresponder groups will be tested with ANOVA (if parametric) or Wilcoxon ranked-sum (if nonparametric). The normality of data will be determined using the Shapiro-Wilk test. Differences will be tested within each time point. Beta diversity differences between response groups will be determined at each time point using PERMANOVA and PERMDISP. Continuous demographic variables (age, BMI, and fiber intake) will be compared with a two-tailed *t* test if parametric and a Wilcoxon rank-sum test if nonparametric, with normality confirmed using the Shapiro-Wilk test. The Fisher exact test will be used to determine the independence of sex, smoking exposure, and race regarding response to treatment. Differences in genera present at >1% average relative abundance will be tested between response groups using a negative binomial model in the MASS package [44].

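### The responder rule has no chance benchmark, and the responder groups are then tested on the same alpha diversity values that formed them

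*Protocol article*

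**What the plan says.** All of this stands in the protocol article, Methods, Response Analysis.

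- **Trigger.** The analysis starts on a condition: "If only a subset of participants is found to respond to the treatment". No criterion is given for finding this.
- **Rule.** Groups are set by each person's "change in alpha diversity metrics across the treatments". The condition for a positive label is: "alpha diversity (either Chao1, Shannon, or inverse Simpson) is greater at time points B and D (whole wheat) than at both A and C". On the literal wording, any one index suffices. There is no minimum change and no allowance for week-to-week variation.
- **Everyone else.** "if this change is not observed, participants will be considered" nonresponders.
- **Test.** "After post hoc assignment of response groups, differences in overall alpha diversity between positive responder and nonresponder groups will be tested with ANOVA", or with a rank test if the data are not normal. A later sentence places these tests within each time point.
- **Further comparisons.** The same two groups are compared on beta diversity, genera, age, BMI, fiber intake, sex, smoking exposure and race.

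Elsewhere, the Design section gives four stool samples per participant, Setting and Participant Recruitment gives 30 adults, and Outcomes names alpha diversity as the primary outcome.

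**The concern.** There are two separate problems.

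First, the rule depends only on the order of four single-sample values, so some people meet it by chance. Allowing any of three related indices raises that share. Without a benchmark, a reader cannot tell a count of, say, eight responders from noise.

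Second, the label is computed from alpha diversity at A, B, C and D, and alpha diversity at A, B, C and D is then tested between the labelled groups. Responders were selected for high values at B and D and low values at A and C. A difference at those weeks is partly built in, and the usual p-value does not allow for that.

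At stake is a secondary claim on the primary outcome variable: a trial with no overall effect could still report a responder subgroup whose diversity differs significantly.

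**Working it through.** The plan states no responder rate or error rate for this rule, so there is no figure of its own to reproduce.

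**Inputs from the protocol article:** 4 time points, 3 indices with any one sufficient, 30 participants, tests within each time point.

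**Assumptions, none of them in the document:** correlations between the indices, serial correlation between weeks, and the within-person correlation (the share of variance that lies between people). Ranges are shown for each.

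**Step 1. One index, no effect, exchangeable weeks.** The two highest of four values must fall on B and D. Probability = 2!·2!/4! = 4/24 = 1/6. Expected in 30: 30 × 1/6 = 5. Probability of no chance responder among 30: (5/6)^30 = 0.0042.

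**Step 2. Any of three indices.** If independent: 1 − (5/6)^3 = 0.421, or 12.6 of 30. For correlated indices, simulation of null multivariate normal data (400,000 participants per scenario; 200,000 or more with serial correlation) gives:

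| Index correlations | Exchangeable weeks | Serial 0.3 | Serial 0.5 |
|---|---|---|---|
| all 0.3 | 38% | 32% | 29% |
| all 0.5 | 35% | 29% | 27% |
| all 0.7 | 31% | 26% | 24% |
| all 0.9 | 25% | 21% | 19% |
| Chao1-Shannon 0.5, Chao1-inverse Simpson 0.3, Shannon-inverse Simpson 0.8 | 33% | 28% | 25-26% |

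Four unequal patterns of the kind in the last row gave 30-33% with exchangeable weeks and 23-28% with serial correlation. On one index, serial correlation lowers the rate from 16.7% to about 13.3% (0.3) or 11.9% (0.5).

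**Step 3. The circular test.** Several thousand null trials of n = 30 were simulated with index correlations 0.5/0.3/0.8. Responders were assigned by any-of-three, then a two-group t test on Shannon (equal to a two-group ANOVA) was done at each week at two-sided 0.05. The last column is the same four tests on randomly formed groups.

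| Within-person correlation | One week | At least one of four weeks | At least one of four, random groups |
|---|---|---|---|
| 0.3 | about 25% | about 71% | about 17% |
| 0.5 | about 19% | about 56% | about 15% |
| 0.7 | about 13% | about 37% | about 13% |
| 0.9 | 7-8% | about 18% | about 11% |

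**Step 4. What is not inflated.** In the same null trials, a covariate unrelated to diversity differed between the groups in about 5% of trials. So did each person's mean Shannon over the four weeks (about 5-5.7%).

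**Step 5. A reference for the count.** With one index and 30 completers, the count is Binomial(30, 1/6): P(9 or more) = 0.051 and P(10 or more) = 0.020.

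**The case against.** The strongest defence is that the section is conditional, openly calls the assignment post hoc, and leaves the primary comparison untouched: Statistical Analyses compares alpha diversity across treatments in all participants. That stands, and it limits the weight of the point. It does not make the p-value of a circular test valid, and the section specifies the rule and the test itself rather than leaving them to another document.

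The size also depends on unstated quantities. If differences between people dominate, the inflation is small (7-8% per week at a within-person correlation of 0.9). If the three-index wording meant one chosen index, the chance rate would be 1/6.

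A reader might infer more than the document supports:

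- **That a third of participants are chance responders.** This is a mid-range value under assumed index correlations and exchangeable weeks, not a figure the document fixes.
- **That the trigger is practically always met.** This holds if the trigger means that at least one person satisfies the responder rule, but the section does not say so.
- **That the search for predictors is inflated too.** Tests of unrelated baseline characteristics keep their nominal error. The weakness there is interpretive: with no effect, they look for correlates of a chance label.
- **That the groups will almost always differ on change in diversity.** No between-group test of change in alpha diversity is planned.
- **That every reading of overall alpha diversity is circular.** A four-week mean would not be inflated. The section, however, places the tests within each time point.

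**Conclusion.** The point holds as a should-fix. The circularity follows from the wording alone, and the one-index chance rate of 1/6 is exact for exchangeable weeks. The other sizes are ranges. Any-of-three labels about 25-38% by chance for index correlations of 0.9 to 0.3 (42% if independent), and less with serial correlation. Single-week false-positive rates run from about 25% down to 7-8% as the within-person correlation rises from 0.3 to 0.9. All of these assume no wheat effect, normal data, and no shift shared by all participants in a given week. The primary comparison is unaffected.

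**What to change.** 1. Define response on one index, named before responder counts are examined. Samples were collected in 2019, so if the counts have already been seen, say so and report the count for each of the three indices.
2. Report the responder count beside its chance reference: 1/6 of those with all four samples, under exchangeable weeks. For 30 completers, 10 or more gives one-sided P = 0.020. State the assumption, and recompute the cut-off for the actual number of completers, since the article itself expects that dropout may occur. Positive serial correlation of the kind simulated lowers the true chance rate, so 1/6 would then be a cautious reference.
3. Replace the tests of alpha diversity between response groups at each time point with descriptive summaries without p-values.
4. Label the remaining comparisons between response groups exploratory.

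The correlation of (B−A) with (D−C) across participants may be shown as a descriptive check on whether response is consistent. It should not be a gate. If people do not differ in response, its expectation is zero only for exchangeable weeks; with first-order serial correlation ρ it is −ρ(1−ρ)/2, that is −0.105 at 0.3 and −0.125 at 0.5. The two pairs also test different wheats, which the Objectives expect to act differently, so a real response to one wheat alone could leave the pairs uncorrelated.

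The cost is analysis wording and the loss of a possible responder p-value. No new data are needed.
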